### Data sources and data collection

#### Data sources

Three types of data sources are considered (Table 1):

**Table 1 Tab1:** Summary of Stroke Patient Data Collection – PAPASéPA

	Inclusion visit	Follow-up at 3 months post-stroke	Follow-up at 1 year post-stroke
Verification of eligibility criteria	✓		
Patient information^1^ + Oral consent	✓		
Data on the care, socio-demographic and clinical pathways (history, severity, complication during the stay ...) to the acute phase (pre-hospitalization and hospitalization) from the ObA2 Observatory ^2^	✓		
Hospitalization data, consultations, acts, outpatient care from the SNDS^3^	Continuous collection		
Clinical data (ad hoc collection):			
- Severity of stroke: NIHSS at discharge	✓		
- Risk factors (alcohol)	✓		
Stroke pathways data (ad hoc collection)^4^			
- Patient referral ^4^	✓		
- Level of education ^5^	✓		
- Professionnal activity ^5^	✓		
- Marital status ^5^	✓	✓	✓
- Cohabitation status ^5^	✓	✓	✓
- Ability to drive ^5^	✓	✓	✓
- Place of life ^5^	✓	✓	✓
- Participation in a therapeutic education program ^5^		✓	✓
- Medical and social care ^5^		✓	✓
- Allowances for disability ^5^		✓	✓
- Family/Caregiver ^5^		✓	✓
- Development and technique to improve autonomy and home care ^5^		✓	✓
- Technical assistance for walking ^5^		✓	✓
- Legal background ^5^		✓	✓
Sequelae post-stroke (ad hoc collection)			
Cognitive disorders (TICS*) ^5^		✓	✓
Anxiety-depressive disorders (HADS**)(Self-assessment)^6^		✓	✓
Fatigue (FSS***) (Self-assessment)^6^		✓	✓
Activity limitations (BI ǂ) (Self-assessment)^6^	✓	✓	✓
Activity limitations (MRSǁ) ^5^	✓	✓	✓
Participation restriction (CIQ-R§) (Self-assessment) ^6^		✓	✓

*Telephone Interview for Cognitive Status; **hospital anxiety and depression scale; ***Fatigue Severity Scale; ǂBarthel Index; ǁmodified Ranking scale; §Community Questionnaire

^1^ Address; telephone number

^2^ Type of stroke; Severity (NIHSS) at admission; Gender; Age; History of Neuro-cardiovascular; History of neuropsychiatric disorders; Anticoagulant / antiaggregant treatments; Rankin before stroke; Date/time start of symptoms; Date/ time call to general practitioner; Date/time call to emergency medical services; Place of occurrence of the stroke; Mode of transport; Date/time of admission to hospital; Type of hospitalization unit; Performing thrombolysis / tele-thrombolysis / thrombectomy; Type of antithrombotic treatment; Complication during stay; duration of stay

^3^ Number / type / duration of hospitalization in medicine or surgery, rehabilitation, psychiatry departments. Hospitalization at home; Number / type of medical and paramedical consultations at hospital; Medical ambulatory care: number / type of medical consultations (general practitioner, neurologist, functional rehabilitation physician, cardiologist) and number of care periods, total duration of each care period / type of paramedical consultations (physiotherapy; speech therapy; orthopsy); Quantity of drug deliveries (antiaggregant, antihypertensive, statin or anticoagulant treatment, analgesic), external medical consultations for neurology, rehabilitation, cardiology in health institutions; Vital status of patients

^4^ Patient referral (admission to the hospitalization area of the institution, transfer to another institution), Level of education (INSEE classification); Marital status (Married - Accessed - Partner; Separated - Divorced – Widowed; Single); Cohabitation status (couple; in family- friends; institution), Ability to drive (yes, no); Place of life (home, institution, medico-social structure), Medical-social care (services to support social life, services to help and support at home, services to provide nursing care at home, services to provide medical and social support), Family/Caregiver (yes, no); Development and technique to improve autonomy (yes, no); Legal background (Curatorship, Guardianship)

^5^ Data collected by telephone by the nurse

^6^ Postal delivery to the participant’s home

Extraction of data from two existing databases: the ObA2 cohort and the French National Health Data System (*Système National des Données de Santé* – SNDS). The extractions from existing databases will provide the main information about care pathways, patient characteristics and stroke characteristics.

The extraction from the ObA2 database will provide information about patient socio-demographic characteristics (date of birth, sex, place of residence), clinical (medical history, risk factors, medical treatment before hospital, type of stroke) and acute phase pathways (pre-hospital: date/time start of symptoms, date/time call to general practitioner, date/time call to emergency medical services, place of occurrence of the stroke, mode of transport, date/time of admission to hospital; hospital stay: initial stroke management, complementary investigations, in-hospital complications, hospital rehabilitation and medico-social care; at discharge: NIHSS, medical treatment at discharge, patient referral) (Table 1).

The National Health Data System regroups healthcare reimbursement data from in-patient and outpatient care, as well as causes of death. It provides data on claims paid for each patient by the French National Social Security System and is therefore the main source of information on healthcare costs. This database contains patient data (age, sex, place of living, long-term and chronic diseases, date of birth, date of death, health insurance scheme, benefit of free complementary insurance for lower-income people), all consultations and visits to General Practitioners (GPs) and ambulatory care specialists (but nothing about their content), all medical technical procedures, all dispensed medical devices and drugs, all lab and diagnostics tests but not their results, and providers’ level data (their activity and sales turnover, geography, prescribing behaviour). In addition, mortality and cause of death data are also available in this database.

Extractions from the SNDS will cover the time period from September 2019 to August 2020 and provide information about the post-stroke care pathway (Table 1):
◦ Number / type / duration of hospitalization in medicine or surgery departments, rehabilitation department, psychiatry department and hospitalization at home. Hospitalisations will be classified into three categories corresponding to hospital stays with different clinical meanings with regard to the evolution of stroke (readmission for management of stroke recurrence and post-stroke complications, readjustment for post-stroke follow-up and secondary prevention of stroke and re-hospitalizations to manage a clinical situation not related to stroke);◦ Number / type of medical and paramedical consultations at hospital;◦ Medical ambulatory care: number / type of medical consultations (general practitioner, neurologist, functional rehabilitation physician, cardiologist) and of paramedical consultations (physiotherapy, speech therapy, orthopsy), number of care periods, total duration of each care period;◦ Quantity of drug deliveries (antiaggregant, antihypertensive, statin or anticoagulant treatment, analgesic);◦ Vital status of patients.

**Ad hoc collection** at any of three points in the study (initial episode, at 3 months and 1 year after the initial episode).

The collection time for each variable is specified in Table 1. The categories of variables collected are as follows:
◦ **Clinical data:** risk factors (Alcohol), severity of stroke at discharge (NIHSS)◦ **Stroke life pathways data:** patient referral, level of education, marital status, cohabitation status, professional activity, ability to drive, place of life, participation to a therapeutic education program, medical and social care, allowances for disability, presence of family and caregiver, development and technique to improve autonomy and home care, technical assistance for walking, legal background.◦ **Post-stroke sequelae assessment**

A selection of scales measuring each of the dimensions explored in our project was selected, based on elements of feasibility, frequency of use in the exploration of the dimension considered and metrological performance (validity and reproducibility): The mode of collection of sequelae has been adapted according to the validated mode of administration for each of the scales. The following sequelae are assessed:
**Cog impairment** using the **French Telephone Interview for Cognitive Status Modified (F-TICS-m).** The TICS scale is a tool for screening for memory disorders. It evaluates time orientation, spatial orientation, immediate memory, calculation, semantic memory, delayed recall, language, understanding of an instruction. Cut offs of 24 and 34 are used (a score less than 24 corresponds to dementia, a score between 24 and 33 corresponds to mild cognitive impairment and a score more than 34 corresponds to a normal condition). This scale was validated in French by telephone [19].**Depression and anxiety** using the **hospital anxiety and depression scale (HADS)**. The anxiety and depression score through the HADS seeks to identify an anxiety-depressive symptomatology and assess its severity. It is composed of 14 items divided into 2 scores of seven items each: a depression score (one for dysphoria, one for deceleration and five for the anhedonic dimension) and an anxiety score. Each item is rated from 0 to 3, allowing to obtain 2 scores. The maximum score for each score is 21. This scale was validated in French by telephone and in a self-administered collection mode [20].**Fatigue** using the **Fatigue Severity Scale (FSS).** The fatigue score through the FSS measures the impact of fatigue on different functions. This is a short questionnaire of nine questions, to which the patient answers on a scale from 1 to 7. The overall score is the average of all the scores obtained on each of the 9 questions. The higher the result, the greater the fatigue. A threshold of 5.5 is often used to differentiate high and low fatigue. This scale was validated in French in a self-administered collection mode [21].**Genito-sexual disorders** using closed-ended question “yes/no”.**Limitations of activities** using the **modified Rankin Scale (mRS)** [23] and the **Barthel Index (BI)** [22]. The modified Rankin Scale (mRS) and the Barthel Index (BI) are commonly used scales measuring the actual abilities of the stroke patient in the basic activities that determine autonomy. The mRS is a more global scale, which measures functional independence rather than the performance of specific tasks. In this way, mental as well as physical adaptations following neurological deficits are assessed. The scale consists of 7 levels, from 0 to 6, with 0 corresponding to no symptoms and 6 corresponding to death. Cut offs of 2 is used (a score less than or equal to 2 corresponds to independence, a score greater than 2 corresponds to dependence). This scale was validated in French by telephone and in self or hetero-administered data collection mode. The IB was developed in 1965 [22] and later modified by Granger and colleagues [43] to measure patient performance in 10 activities of daily living. The IB is considered a sensitive and reliable disability scale for stroke patients. The IB items can be divided into two groups: one, related to self-care (diet, grooming, bathing, clothing, urinary and anal continence, and toilet use) and the other, related to mobility (ambulation, transfers and stair climbing). The maximum score is 100, which indicates that the patient is totally independent in physical functioning. The lowest score is 0, which represents a totally dependent bedridden state. A dependency to consider a return home is usually defined by a score greater than or equal to 60. The IB is a scale validated in French in a data collection mode by interview (hetero-administered).**Participation restrictions** using the **Community Integration Questionnaire (CIQ)**. The CIQ assesses disability for brainy people in three areas: home integration (active participation in the functioning of the home or household), social integration (participation in social activities outside the home), productivity (regular work performance). It is composed of three sub-scores: home integration [0–12], social integration [0–10], productivity [0–7]. The total CIQ score [0–29] is the sum of the 3 sub-scores.

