### Predictive factors and outcome

Many studies have analyzed the stroke functional predictive factors [24, 25]. They can be sorted into three categories: variables related to the patient’s previous condition (age, sex, patient history, antecedents and autonomy before stroke), variables related to stroke (severity of hemiplegia, type of stroke - cerebral infarction or intracerebral hemorrhage) and finally variables related to the patient’s life pathways (speed of care in the acute phase, access to a stroke unit, early return home, social and familial environment). These factors interact with each other.

Among the variables related to the patient’s previous state, it is established that the autonomy, assessed by the modified Rankin score or the Barthel index, prior to stroke and at the inaugural event, is decisive in term of functional outcome.

Among the variables related to stroke, the initial severity of stroke, measured by the Institutes of Health Stroke Scale (NIHSS) [26], is one of the variables most strongly associated with the functional outcome.

With regard to the elements of the care pathway, several studies have showed that short and long-term outcomes after stroke are associated with better acute care, such as thrombolysis and stroke unit care, as well as risk factor management before and after stroke. As regards post-stroke pathways and outcome, only the role of rehabilitation treatment after a stroke [27–30] and the early supported discharge [31–34] have been shown as linked to functional outcomes. Reeducation must be initiated in stroke units, according to the patient needs, and continued and coordinated by a multidisciplinary team. However, no information exists on the functional role of further temporal and spatial elements of the downstream pathways following stroke.

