#### Statistical analysis

##### Analysis strategy

The analysis of the assessment criteria will be carried out on available data, i.e. without any replacement of missing data. For the analysis of the primary endpoint, a sensitivity analysis of missing data, using a multiple imputation method, may be considered. The analysis will be carried out using the SAS 9.3 software (or later version) considering a risk of first species fixed at α = 5%. A statistical analysis plan will be defined blind data.

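### The printed categories for cohabitation status have no code for a patient living alone at home, and no other listed variable supplies that information

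*Protocol article*

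**What the plan says.** Table 1 of the protocol article lists "Cohabitation status" among the stroke pathway data, collected by the nurse at inclusion, 3 months and 1 year. The text under Data sources confirms that the table governs timing: "The collection time for each variable is specified in Table 1". Footnote 4 gives the categories, together with those for driving and place of life: "Cohabitation status (couple; in family- friends; institution), Ability to drive (yes, no); Place of life (home, institution, medico-social structure". The same footnote gives those for marital status, "Marital status (Married - Accessed - Partner; Separated - Divorced – Widowed; Single". It also lists family or caregiver as a yes/no item, which Table 1 schedules at 3 months and 1 year only.

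The section on predictive factors counts among the pathway-related predictors of functional outcome "early return home, social and familial environment". The Objectives make pathway components the exposures of the main objective, and make a pathway typology and the analysis of social and geographical inequalities secondary objectives. The section on the perimeter of life pathways says that family and social environment will be taken into account. On missing data, the Analysis strategy states: "The analysis of the assessment criteria will be carried out on available data, i.e. without any replacement of missing data". It adds that multiple imputation may be considered as a sensitivity analysis for the primary endpoint.

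**The concern.** A set of response categories for an exposure should cover every patient. This one covers people living with a partner, people living with relatives or friends, and people in an institution. A single, divorced or widowed person living alone in their own home fits none of the three. The nurse who follows the printed list must leave the item empty or choose a category that is untrue.

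Living alone is one of the plainest expressions of the social and family environment that the study sets out to examine. If it is never recorded as such, no later analysis can recover it, whether the outcome is the modified Rankin score or another sequela. The gap also falls on one defined social group and not at random.

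**Working it through.** No figure in the plan is in dispute, so the check is a comparison of the listed variables.

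**Step 1: does the list cover all living situations?**

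| Situation | Cohabitation code as printed |
|---|---|
| At home with spouse or partner | couple |
| At home with children, other relatives or friends | family/friends |
| In a care institution | institution |
| At home, alone | none |

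**Step 2: can another listed variable stand in?**

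- Marital status is legal or partner status. A widowed patient may live alone or with children.
- Family/caregiver (yes, no) records support and not co-residence, and is not scheduled at inclusion.
- Place of life, coded as home, does not say who else lives there.
- The ObA2 items described under Data sources are date of birth, sex, place of residence, clinical data and acute-phase data. The SNDS items are demographic, insurance, care-use and death data. Neither list includes household composition.

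**Step 3: do the variables jointly identify living alone?** Take two widowed patients, both at home and both with a daughter as caregiver. The first lives alone and the daughter visits; the second shares a home with the daughter. They have identical values for marital status, place of life and family/caregiver. Only cohabitation could separate them. The second is coded family/friends; the first has no code.

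**Step 4: what follows for the analysis?**

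- *Item left blank.* A blank for living alone cannot be told apart from a refused or unknown answer. With no replacement of missing values, these patients leave any model that contains cohabitation. Imputation does not help: it can draw only from categories that someone was recorded in, and nobody is recorded as alone.
- *Item forced.* Suppose a proportion m of those coded family/friends actually live alone, with mean outcome (on the model's scale) A for those living alone and F for those truly with family or friends. The category then shows (1 − m)F + mA. It differs from the true F by (1 − m)F + mA − F = m(A − F). The family/friends result is distorted and A itself is never estimated. The documents give neither m nor A − F, so this shift cannot be put in numbers.

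In both cases living alone is unavailable as an exposure, as an input to the clustering described in the Analysis plan, and as a social characteristic to compare between pathway types.

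**The case against.** The strongest reply is that the footnote is not a complete code list. Legal background shows two protective measures and no entry for neither. Medical-social care names four services and no entry for none. Patient referral names admission and transfer but not return home. The default value is often left out, and living alone may be another such omission. This is a journal article, and the case report form and telephone script are not shown.

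Part of this stands: nobody can conclude from the article that the form lacks the code. It does not remove the point. A blank under legal background reads naturally as neither measure. Cohabitation is laid out as a set of alternatives, extending even to people in institutions, and the marital list beside it does name the single. An empty cohabitation item has no such natural reading.

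Three stronger conclusions might be inferred, and the documents do not support them.

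- *Patients in hospital or rehabilitation have no place-of-life code.* Institution is listed separately from medico-social structure, and the same footnote uses the word for a hospital when describing referral. Place of life can also be read as residence and not current stay. Number, type and duration of rehabilitation stays come from the SNDS in any case. At most the boundary of institution is undefined.
- *The institution option under cohabitation is redundant with place of life.* People in institutions need a cohabitation code, so the overlap is not a fault.
- *The study loses a stated number of patients or a stated amount of power.* This needs a share living alone, which the documents do not give. It also needs the item to be blank and in the model. Models of other pathway components that omit cohabitation are unaffected.

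**Conclusion.** The point holds for cohabitation status alone. As printed, the list is not exhaustive, and no other listed variable recovers the missing state at any of the three time points. If data are collected that way, the comparison of patients living alone with others is lost entirely, whatever their share. The number of patients concerned is unknown from the documents, and the planned sample size is not called into question.

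The conclusion assumes that the printed list is the list in use. If the form already has the code, only the published footnote needs correcting. A reader might also infer that the social-inequality objective fails as a whole. It does not: education, marital status, place of residence and the SNDS marker of complementary insurance for people on low income remain. What is missing is one social characteristic that the study's own rationale makes relevant.

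**What to change.** Change the cohabitation categories in Table 1, footnote 4, to: alone; with spouse or partner; with other family or friends; institution. Use the same list at inclusion, 3 months and 1 year, and confirm that the case report form and telephone script carry it. If the form already has a code for living alone, state in the footnote how it is coded. Keep a separate missing or not-known code, so that an empty item is never read as living alone.

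The cost is one response list on the form and in the script, with no extra visit, staff or question.

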## Methods/design

### Study design

The study design is an observational prospective cohort of stroke patients included in ObA2 with a patient follow up period for 1 year following stroke. Continuous data collection of care pathways will be carried out from stroke throughout the year of follow-up from existing databases (the ObA2 data base and the French National Health Data System (*Système National des Données de Santé -* SNDS); moreover, ad hoc collection of sequelae, pathways and socio-economic and environmental data is planned at three times (initial episode, at 3 months and 1 year after initial episode) (Fig. 1). The cohort is divided into three strata based on the severity of the patient’s initial clinical condition, as measured by the NIHSS score (≤6, [7–16], > 16) at the end of the hospital stay (Fig. 1).

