#### Patient selection criteria

The inclusion criteria into the PAPASéPA cohort are: inclusion criteria to ObA2 (being over 18 years of age living in metropolitan France, suffering from a recent stroke whose diagnosis was confirmed by a neuro-vascular physician) and as additional criteria, Giving consent to participate to PAPASéPA).

Patients will be identified prospectively as they are included in ObA2. The inclusions will be carried out continuously and prospectively from the date of the beginning of inclusions (planned to be in september 2019) until the required number of subjects is obtained in each strata.

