##### Classification of hospitalizations during the following year

For all included patients, the re-hospitalizations in medicine or surgery departments that took place during the year of follow-up will be identified from the SNDS base and classified into three categories: 1) readmission for management of recurrence and post-stroke complications; 2) readjustment for post-stroke follow-up and secondary prevention of stroke and 3) re-hospitalizations to manage a clinical situation not related to stroke.

This classification will be carried out in three stages: 1) automated classification based on ICD-10 codes and procedures associated with readmission, 2) for re-hospitalizations not classifiable in an automated way, the IRC will return to the corresponding patient record, within the hospitalization facility and 3) if it is impossible for IRC to classify rehospitalization, a group of experts (including 3 neurologists and a rehabilitation doctor) will meet to classify each remaining hospitalization, based on the information from the hospitalization report.

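### The fixed SNDS window, September 2019 to August 2020, contradicts open-ended inclusion from September 2019 and the one-year database follow-up promised for each patient

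*Protocol article*

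**What the plan says.** In the protocol article, the Data sources section sets the extraction by calendar: "Extractions from the SNDS will cover the time period from September 2019 to August 2020". The same sentence gives its purpose as the care pathway after stroke. The items listed are hospital and rehabilitation stays, consultations, paramedical care, drug deliveries and vital status.

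Patient selection criteria makes entry staggered: "The inclusions will be carried out continuously and prospectively from the date of the beginning of inclusions". The start is "planned to be in september 2019) until the required number of subjects is obtained in each strata". No closing date is given.

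The Study design section describes a cohort "with a patient follow up period for 1 year following stroke" and adds: "Continuous data collection of care pathways will be carried out from stroke throughout the year of follow-up from existing databases". Table 1 marks the SNDS items as continuously collected.

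For all included patients, the section on classifying hospitalisations says that "the re-hospitalizations in medicine or surgery departments that took place during the year of follow-up will be identified from the SNDS base". The Outlook section likewise chains hospital stays from the acute episode to one year after stroke. The procedure for patients lost to follow-up uses the SNDS links to find in-hospital deaths among those who could not be reached at 3 months or 1 year.

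Nothing in the article extends or qualifies the calendar window.

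**The concern.** A window of 12 calendar months that opens in the month inclusion opens can hold a full year only for the very first patients. Everyone later is cut off at the end of August 2020, and anyone whose stroke falls after that date has no SNDS data.

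The length of observation in the SNDS would then depend on the date of inclusion. Counts and durations of stays, consultations, paramedical care and drug deliveries would not be comparable between patients. A typology that uses them could partly separate early from late entrants. Because inclusion continues until each NIHSS stratum is full, a slower-filling stratum has later entry dates and loses more. Truncation would then be tied to discharge severity, which the article itself treats as a major potential confounder (Justification of methodological choices, Study design). The re-hospitalisation classification and the SNDS part of the death search would stop at the same date.

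**Working it through.** **Inputs from the article**
- Extraction window: September 2019 to August 2020 (Data sources).
- Inclusion: from September 2019, open-ended (Patient selection criteria).
- Follow-up: 1 year per patient from stroke (Study design).
- Planned total: 1210, from 3 × 368 = 1104 plus an allowance for loss (Sample size selection).
- Volume of the 13 centres: 5230 stroke patients in 2016 (Representativeness of cohort).

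**Input assumed:** accrual is uniform over A months. The article gives no accrual length, so A is varied. A month is taken as 30.4375 days.

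**Step 1, the window.** At its widest, 1 September 2019 to 31 August 2020 is 366 days (2020 is a leap year). A stroke t days after 1 September 2019 has max(0, 366 − t) days of SNDS data. A full 365 days needs t ≤ 1, so only strokes on about the first two dates qualify. A patient included in early September after a late-August stroke would instead lack the first days.

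**Step 2, the shortest possible accrual.** 5230 / 12 = 435.8 patients a month, and 1210 / 435.8 = 2.8 months. This requires every stroke patient in the 13 centres to take part and no stratum to slow inclusion, so it is a floor and not a forecast.

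**Step 3, coverage.** Let D = 30.4375 × A be the accrual period in days.
- If D ≤ 366, mean coverage is 366 − D/2.
- If D > 366, mean coverage is 366² / (2D).
- The share of planned person-time is mean coverage / 365.
- The share of patients with a full year is about 1/D.

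Worked cases:
- A = 2.8: D = 84.5; 366 − 42.3 = 323.7; 323.7 / 365 = 0.887.
- A = 6: D = 182.6; 366 − 91.3 = 274.7; 274.7 / 365 = 0.753.
- A = 12: D = 365.25; 366 − 182.6 = 183.4; 183.4 / 365 = 0.502.
- A = 18: D = 547.9; 133,956 / 1095.8 = 122.2; 122.2 / 365 = 0.335.

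| Accrual (months) | Person-time captured | Mean months of SNDS data | Patients with a full year, of 1210 | Window end needed |
|---|---|---|---|---|
| 2.8 (floor) | 89% | 10.6 | about 14 (1.2%) | 23 Nov 2020 |
| 6 | 75% | 9.0 | about 7 (0.5%) | 1 Mar 2021 |
| 12 | 50% | 6.0 | about 3 (0.3%) | 31 Aug 2021 |
| 18 | 33% | 4.0 | about 2 (0.2%) | 1 Mar 2022 |

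At 12 months of accrual about 25% of patients have less than 3 months of SNDS data. At 18 months about 33% have none: (547.9 − 366) / 547.9 = 0.33.

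**Step 4, does any accrual length rescue the dates?** No. Even at the floor, the window would have to run to late November 2020. The contradiction does not depend on A; only the amount lost does.

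**The case against.** The best defence is that one date clause stands against several sections that state a one-year follow-up per patient. It may be a drafting slip, or the dates may have been meant as the period of index strokes, with a further year extracted for each patient. That is plausible, but the article attaches the dates to the extraction of post-stroke care data, not to the index strokes. The sentence needs correcting on either reading, and an index period with a fixed end would still not fit an open-ended inclusion rule.

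The rest of the defence limits the consequences, and it stands. A reader might infer more than the article supports in five ways:

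- **That the primary analysis loses its main exposures.** The primary objective concerns life-pathway components, and the section on their perimeter says these come mainly from telephone interviews. Acute-phase items come from ObA2. The SNDS supplies the post-stroke care-pathway part.
- **That the primary outcome is truncated.** The mRS at 3 months and 1 year is collected by telephone, outside this window. SNDS exposure up to 3 months would also be complete for strokes until about the end of May 2020.
- **That deaths are broadly missed.** The research nurse first contacts the treating physician or people close to the patient. The SNDS search is an addition and covers only deaths during a hospital stay.
- **That the most severe stratum would take a known, long time to fill.** The article gives neither the share of patients discharged with NIHSS above 16 nor a consent rate, so no fill time can be derived.
- **That truncated patients would be analysed as non-users of care.** This depends on how unequal observation time is handled, which may be set out in an analysis plan not shown here.

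**Conclusion.** The point holds as an internal contradiction that gives a wrong result if followed. The stated extraction window is incompatible with the inclusion rule and with the promised year of database follow-up. Taken literally, at most about 1% of patients have a full year of SNDS data. This is not detail left out of a condensed article: a window is stated, and it conflicts with other sections.

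The loss of person-time runs from about 11% at the unattainable 2.8-month floor to 50% at 12 months of accrual and 67% at 18. These figures rest on uniform accrual over an assumed length. Heavier truncation in slower strata follows from the inclusion rule, but the article does not allow its size, or which stratum would be slowest, to be stated.

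The damage is confined to SNDS-derived care-pathway variables, the typology to the extent that it uses them, the re-hospitalisation classification and the supplementary search for in-hospital deaths. Survey data and the mRS interviews are intact.

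**What to change.** Replace the calendar dates in Data sources with a per-patient window from stroke date to 12 months after stroke, and state that the extraction ends no earlier than 12 months after the last inclusion. Apply the same window to the re-hospitalisation classification and to the SNDS search for in-hospital deaths, so that these sections agree with Study design. If the dates were meant as the index-stroke period, say so, state the further year of extraction, and reconcile the fixed end with the rule of including until each stratum is full.

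The cost is a corrected sentence, an updated SNDS data request and a later extraction, with no extra patients or visits. The article cites a specific data-protection authorization but does not say whether it fixes extraction dates, so check that it covers the new period.
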